##### Ecological Momentary Assessment Data

The EMA dataset will be structured with study days (level 1 units) nested within couples (level 2 units). Each study day observation will have values for patient and partner reports of afternoon communication (holding back, disclosure, protective buffering, support, perceived partner holding back, perceived partner support) as exogenous predictors, afternoon reports of cognitive processing (avoidance, intrusive thoughts) or intimacy as mediators, and evening reports of psychological distress (POMS TMD composite) or relationship satisfaction as outcomes, all from the same day’s afternoon and evening assessments. In addition, autoregressive associations are included such that afternoon reports of mediators are predicted from the preceding evening’s reports of the same variables (e.g., patient evening report of intimacy on day t-1 predicts patient afternoon report of intimacy on day t) and each evening outcome variable is predicted by the immediately preceding observation on the same variable. See Figure 2 for an example treating intimacy as the mediator and distress as the criterion, with variables and paths of conceptual interest in black, and control variables and paths less central to the conceptual models in gray. Indirect associations of afternoon communication with change in same-day evening outcomes (distress or relationship satisfaction) *via* mediators assessed on that same afternoon will be estimated using a product-of-coefficients approach and evaluated using 95% confidence intervals.

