### Overview

Associations hypothesized under the SCP and RI models will be examined with structural equation models (SEMs) separately for questionnaire data from T1-T4 and data from the EMA phase, primarily in a longitudinal actor-partner interdependence model (APIM) framework, with patients and partners treated as distinguishable dyad members (Ledermann et al., 2011). To examine longitudinal within-couple associations in the questionnaire data, random intercept cross-lagged panel models (Hamaker et al., 2015) will be estimated. EMA data will be analyzed using multilevel SEMs with repeated observations of patient- and partner-reported measures treated as being nested within dyads. Differences in hypothesized associations based on gender and role (patient vs. partner) will be examined using a variety of dyadic and non-dyadic analytic approaches as detailed below. Examination of how different assessments of communication (questionnaire, EMA, and objective assessment) prospectively predict psychological and relationship adjustment at follow-up will also be estimated using SEMs in an APIM framework.

All SEMs will be estimated in Mplus 8.7. Bootstrap standard errors for direct and indirect effects will be estimated, except for multilevel SEMs, where a Monte Carlo simulation approach will be used (see, e.g., Zyphur et al., 2016). For models that prove to be unestimable under maximum likelihood (ML) estimation (e.g., due to computational demands of numerical integration), Bayseian estimation will be used. Models fit using ML will be evaluated using comparative fit index (CFI), root mean squared error of approximation (RMSEA), and standardized root mean square residual (SRMR) values, with CFI > 0.95, RMSEA ≤ 0.06 (with upper confidence limit ≤ 0.08), and SRMR < 0.08 as benchmarks for acceptable model fit (Hu and Bentler, 1999). For models fit using the Bayes estimator, Bayesian versions of CFI and RMSEA values (Asparouhov and Muthen, 2021) will be examined.

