In line with the general APIM framework, both prospective actor (within-person, cross-construct) effects (e.g., *patient* communication predicting *patient* intimacy) and prospective partner (between-person, cross-construct) effects (e.g., *patient* communication predicting *partner* intimacy) will be estimated along with autoregressive (prospective within-person, within-construct) associations. Mediators and outcomes will be treated as manifest variables in these models. Latent person-level intercept factors will be included to account for random between-person variability in mean levels of model constructs. Within-couple indirect associations of communication and outcomes (psychological distress or relationship adjustment) *via* mediators (e.g., actor-actor effects and partner-actor effects) will be estimated using a product-of-coefficients approach (MacKinnon et al., 2007) and evaluated using 95% confidence intervals.

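### The EMA mediator equation, as the text writes it, names no lag of the previous evening's distress or satisfaction, so carry-over can bias the communication-to-mediator path

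*Protocol article*

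**What the plan says.** The section on Ecological Momentary Assessment Data sets out one row per study day within couple. Both members' afternoon communication reports enter "as exogenous predictors, afternoon reports of cognitive processing (avoidance, intrusive thoughts) or intimacy as mediators", and evening distress or relationship satisfaction is the outcome.

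Two lagged controls are written:
- For the mediator: "afternoon reports of mediators are predicted from the preceding evening’s reports of the same variables". The text illustrates this with intimacy: "reports of the same variables (e.g., patient evening report of intimacy on day t-1 predicts patient afternoon report of intimacy on day t".
- For the outcome: "each evening outcome variable is predicted by the immediately preceding observation on the same variable".

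Indirect associations through "mediators assessed on that same afternoon will be estimated using a product-of-coefficients approach and evaluated using 95% confidence intervals".

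The section then refers to Figure 2 for an example with intimacy as mediator and distress as criterion, drawn "with variables and paths of conceptual interest in black, and control variables and paths less central to the conceptual models in gray". The control paths in gray are not listed in the text.

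For the questionnaire data, the Overview names "random intercept cross-lagged panel models", and the Questionnaire Data section describes "both prospective actor (within-person, cross-construct) effects" together with partner and autoregressive effects.

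**The concern.** Communication and mediator are reported at the same afternoon prompt. The communication-to-mediator path (a) is therefore contemporaneous, and its interpretation depends on what is held fixed from the evening before. Both lags in the text are same-variable lags.

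A distressed or unhappy evening could plausibly reduce next-morning disclosure and also reduce closeness or raise intrusive thoughts, over and above the previous evening's closeness or intrusions. It would then be a common cause of communication and mediator that the written mediator equation leaves open.

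The two outcomes differ slightly. Distress is asked at both prompts, so its immediately preceding observation is the same afternoon's, and the previous evening's distress is named nowhere. Satisfaction is asked only in the evening (Table 2), so its previous-evening value enters the outcome equation but is not named in the mediator equation.

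What is at stake is Aim 1's day-to-day test of the two models. The Introduction faults earlier mediation studies for being unable to establish direction and offers EMA as capturing temporal sequence. Carry-over of mood from one day to the next is one of the rival explanations that such a design is meant to remove.

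**Working it through.** The plan states no figure for this analysis. Its only power statement (264 dyads retained of 434, power 0.80) concerns the questionnaire data, so there is nothing to reproduce first.

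**Inputs from the protocol article.** Two prompts a day for 14 days leave 13 days with a previous evening. No EMA sample size is given, so the questionnaire figures are borrowed: 264 × 13 = 3,432 couple-days, or 434 × 13 = 5,642.

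**Assumed inputs (not in the documents).** Effect of the previous evening's outcome on communication (g) and on the mediator (h), equal in size at 0.10 to 0.30; mediator-to-outcome effect (b) of 0.2 or 0.15 in size; residual variances of 1; moderate autoregression.

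**Algebra.** Write C for afternoon communication, M for the mediator and D for the previous evening's outcome. Leaving D out of the mediator equation gives

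bias(a) = h × cov(C, D | lagged M) / var(C | lagged M).

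With C = gD + noise of variance 1 and v = var(D | lagged M), this is ghv / (1 + g²v). In the simulated distress chain v is about 1.36 to 1.38:
- g = h = −0.1: 0.01 × 1.36 / (1 + 0.0136) = 0.013
- g = h = −0.2: 0.04 × 1.37 / (1 + 0.0548) = 0.052
- g = h = −0.3: 0.09 × 1.38 / (1 + 0.1242) = 0.110

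**Simulation A.** 264 couples × 13 days, simplified one-person chain, true a = 0, b = 0.2 in size, 300 replicates, cluster-robust standard errors, Monte Carlo 95% interval for a × b.

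| Outcome | Carry-over (size of g and h) | Mean a, as written | Interval excludes 0, as written | Interval excludes 0, lag added |
|---|---|---|---|---|
| Distress | 0.1 | 0.014 | 11% | 4% |
| Distress | 0.2 | 0.052 | 87% | 5% |
| Distress | 0.3 | 0.109 | 100% | 8% |
| Satisfaction | 0.1 | 0.013 | 11% | 5% |
| Satisfaction | 0.2 | 0.054 | 88% | 5% |
| Satisfaction | 0.3 | 0.118 | 100% | 4% |

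The simulated bias matches the algebra. With the lag added, a returns to about 0.

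**When the problem disappears.** At a carry-over size of 0.3 on the remaining path, the equation as written gives 5–7% if the previous evening does not affect communication (g = 0) and 4–6% if it does not affect the mediator (h = 0). With b = 0, a is still biased (about 0.105), but a × b is about 0 and the interval excludes 0 in 3–5% of runs. In every setting b is recovered (about 0.20 in size where that is the truth), because the outcome equation carries its own lag.

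**When mediation is real.** With true a = 0.2 and carry-over of 0.2, the distress indirect effect is 0.051 in size as written and 0.041 with the lag (0.051 / 0.041 = 1.24). For satisfaction the ratio is 0.052 / 0.040 = 1.30.

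**Sensitivity to settings.** Simulation B used 434 couples × 13 days, b = −0.15, half-day stability 0.40, and required both paths to be significant. Simulation C was a further run with 264 couples × 13 days and b = −0.2.

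| Carry-over | B, all prompts answered | B, 85% response with row-wise loss (about 2,100–2,200 rows) | C |
|---|---|---|---|
| 0.10 | 11% | 9% | 8% |
| 0.15 | 33% | 14% | 22% |
| 0.20 | 82% | 34% | 65% |
| 0.30 | not run | not run | 100% |

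Adding the lag gave 4–6% throughout B and about 4–6% in C. Across A, B and C, false mediation is 8–11% at 0.10 and 34–88% at 0.20.

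**The case against.** The strongest objection is that the text may not list every path. It sends the reader to Figure 2 for control variables and paths in gray, and that figure was not available here. A lagged-distress path is the sort of control it could show. A condensed article may also leave the full path list elsewhere. This stands: a reader might infer that the model adjusts for nothing but the lagged mediator, and the documents do not establish that. It does not close the point, because the figure is an example for one pair, intimacy and distress, and would not by itself settle the SCP models or the satisfaction outcome.

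Three other strong readings also fail:
- That a bad evening will be reported as mediation. False mediation needs carry-over to both communication and mediator, plus a real mediator-to-outcome effect.
- That even slight carry-over is enough because there are thousands of rows. At 0.10 about nine in ten simulated studies would not declare mediation.
- That Aim 1 holds its two data sources to different standards. The questionnaire text does not spell out an outcome-to-mediator lag either. That contrast is inferred from the name of the method.

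It is also fair that the simulations are simpler than the dyadic multilevel SEM in the plan, and that the couple numbers come from the questionnaire sample. They show direction and rough scale and do not predict this study's error rate.

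**Conclusion.** The point holds in a limited form. The written mediator equation names only the mediator's own lag, so the communication-to-mediator path is open to carry-over from the previous evening's outcome unless Figure 2 or the full plan already closes it. The defect is confined to that path.

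The consequence depends on a quantity the documents do not give. At an assumed carry-over of 0.10 the excess is small. At 0.20 it is large enough to make a significant indirect effect unconvincing, and a true indirect effect would be overstated by roughly a quarter to 30%. These sizes rest on equal carry-over to communication and mediator, a mediator-to-outcome effect of 0.15 to 0.2 in size, and a one-person simplification of the dyadic model. The change is worth making because it is cheap and removes a rival explanation that the data can address.

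**What to change.** In every EMA mediator–outcome model, add the previous-evening value of that model's outcome, for both dyad members, as a predictor of each member's afternoon mediator. Let it covary with afternoon communication, and read the indirect effect from that model. Alternatively, confirm that Figure 2 already contains this path and state in the text that it applies to all SCP and RI models and to both outcomes.

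Both outcomes are already collected each evening, so no new data are needed. The cost is two further predictors in each of two mediator equations, that is 2 × 2 = 4 paths per model, plus the covariances with communication. The Overview already foresees that some models may not be estimable by maximum likelihood and provides a Bayesian fallback. The change does not remove confounding that arises the same morning, since communication and mediator still come from one prompt, and the report should say so.

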**FIGURE 2 F2:**
[figure not shown]
Illustration of analytic model to examine mediating dyadic processes using ecological momentary assessment data. PT, patient; CG, caregiver. Note. Variables and paths of conceptual interest are in black; control variables and paths less central to the conceptual model are in gray.

#### Differential Functioning of Social-Cognitive Processing and Relationship Intimacy Models by Gender and Role

To examine potential differential functioning of the SCP and RI models across gender (male vs. female) and role (patient vs. partner), we will employ two different modeling approaches within an APIM framework. For gender, we will add gender × communication and gender × mediator (e.g., gender × intrusive thoughts, gender × intimacy) terms to the standard “main effects” APIM models described above. For example, we would examine patient gender × patient communication, partner gender × partner communication, patient gender × patient intimacy, and partner gender × partner intimacy terms in a single model. To examine differential functioning by role, we will examine how individual cross-role equality constraints for parallel APIM actor and partner effects (e.g., patient communication-patient intimacy and partner communication-partner intimacy) affect model fit and test between-role differences in indirect effects. These models will be supplemented by exploratory analyses examining purely within-person (i.e., non-dyadic) models to examine indirect effects and model fit in gender and role group subsamples.

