Another critique of the extant literature in this area is that most studies have employed standard global questionnaire-based measures of communication. It is widely acknowledged that relationships and communication processes are dynamic and can change over time and with circumstances (Lepore and Revenson, 2007; Badr et al., 2013), thus an understanding of these processes requires going beyond the single-time retrospective measures that are commonly used. Ecologically valid approaches offer a number of advantages. We focus here on ecological momentary assessment (EMA). First, EMA minimizes recall biases inherent in global, retrospective measures which require participants not just to remember but also to summarize their behavior. When considering such questions, individuals use a variety of heuristics to estimate their answers, leading to systematic biases influenced, for example, by current mood (Shiffman et al., 2008). Second, compared to both global self-report and laboratory-based assessments, EMA increases ecological validity as participants are reporting in their real-world environment. Third, the longitudinal nature of EMA data can be used to examine temporal sequences of behaviors and experiences (Shiffman et al., 2008). To our knowledge, a handful of studies has employed daily diary approaches to assess constructs relevant to either the RI model (Belcher et al., 2011; Perndorfer et al., 2019) or the SCP model (Pasipanodya et al., 2012; Badr et al., 2013), but they all involved breast cancer samples and were relatively small in size, ranging from 45 dyads (Belcher et al., 2011) to 69 dyads (Perndorfer et al., 2019). Because the majority of breast cancer cases are female, sole focus on this cancer site confounds gender and patient role. In addition, these studies employed electronic diaries but were internet-based vs. smartphone-delivered. Given the ubiquity of cell phones (94%) and in particular smartphones (81%) in the United States (Pew Research Center, 2019), the ease and immediacy of gathering EMA on a device already at hand may facilitate completion and minimize participant burden. This is true for not just younger adults but also persons aged 50 and higher, with smartphone ownership among the latter having increased from 53% in 2015 to 67% in 2018 (Pew Research Center, 2019).

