## Methods and Analysis

### Design and Participants

The study design is longitudinal, with repeated questionnaire-based assessments at baseline and 4, 8, and 12 months post-baseline to capture quarterly reports across a 1-year follow-up period without undue participant burden. Patients are recruited from the Duke Cancer Institute in Durham, NC and the Seattle Cancer Care Alliance in Seattle, WA, two NCI-designated comprehensive cancer care centers. Inclusion criteria for patients are:

•age 18 or older•stage II-IV breast, colon, rectal, or lung cancer•currently receiving or having received a form of systemic therapy (or hormone therapy for breast cancer) within 2 years of diagnosis of current stage•life expectancy of at least 6 months per primary oncologist•ability to speak and comprehend English•being married or in a committed, cohabiting relationship with a same- or opposite-sex partner

We chose to focus on breast, colorectal, and lung cancers because they are relatively common solid tumor cancers and because, with the exception of breast cancer, occur frequently in both males and females.

Inclusion criteria for partners are:

•age 18 or older•ability to speak and comprehend English•being married to or in a committed, cohabiting relationship with the patient

Exclusion criteria are provider non-approval (patients), cognitive impairment prohibiting completion of study assessments (patients and partners), and logistical constraints preventing participation (patients and partners).

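### The aim 2 gender models cannot tell a gender difference in slopes from a breast-versus-other-site difference; add site-based sensitivity analyses

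*Protocol article*

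**What the plan says.** The section on differential functioning by gender and role gives the method: "For gender, we will add gender × communication and gender × mediator" "terms to the standard “main effects” APIM models described above". Its worked example has four terms: patient and partner gender, each multiplied by that person's own communication and own intimacy. The base models, under Questionnaire Data and Ecological Momentary Assessment Data, contain actor, partner and autoregressive paths. The questionnaire models also have random intercepts: "Latent person-level intercept factors will be included to account for random between-person variability". No cancer-site or treatment term is named in any of these sections.

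Design and Participants says that the chosen cancers, "with the exception of breast cancer, occur frequently in both males and females". Its treatment criterion for patients is "currently receiving or having received a form of systemic therapy (or hormone therapy for breast cancer) within 2 years of diagnosis of current stage", so hormone therapy is a named route for breast cancer only. The Introduction criticises earlier work: "Because the majority of breast cancer cases are female, sole focus on this cancer site confounds gender and patient role". The remedy given at the end of the Introduction is to include three cancers that affect both sexes, so that role can be separated from gender. Separating cancer site from gender is not mentioned.

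Medical Record Extraction lists cancer site and systemic or hormone therapy among the data collected. The Discussion says that subgroup differences will guide clinical use of the results.

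**The concern.** Female patients will be a mix of breast and colon, rectal or lung cancer, while male patients will be almost entirely colon, rectal or lung. A gender × communication term in the pooled sample therefore compares two groups that also differ in cancer site and, through the hormone-therapy route, possibly in treatment. In opposite-sex couples a male partner belongs to a female patient, so the partner-gender terms carry the same contrast with the sign reversed. The exploratory gender subsamples have the same mix.

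The random intercepts do not resolve this. They absorb stable differences in level, whereas aim 2 is about differences in slope. At stake is the label on the result: a slope difference that belongs to breast cancer could be read as a difference between men and women, or a true gender difference could be offset by a site difference of opposite sign.

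**Working it through.** **The plan's own figure.** The article states power of 0.80 for an overall indirect effect with 264 dyads, both paths r = 0.25 and confounding R² = 0.15. A Sobel-type approximation gives SE = √[(1 − 0.25²) / (264 × 0.85)] = 0.0646, z = 0.25 / (√2 × 0.0646) = 2.73, and power = Φ(2.73 − 1.96) ≈ 0.78, close to 0.80. Other approximations run from 0.75 to 0.94. This figure concerns overall mediation. No power or target size is stated for gender moderation, so r = 0.25 is not a yardstick for a between-gender difference.

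**Inputs for the check**
- From the article: n = 264 complete dyads; 95% intervals, taken as two-sided 5% tests.
- Assumed, not in the documents: breast share of patients s = 20–60%; all breast patients female; proportion of women at the other sites f = 40–50%; standardised predictor and residual; a slope difference δ between breast and other sites.

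**Bias.** The expected gender × X coefficient is the true gender difference γ plus δ × [P(breast | female) − P(breast | male)]. With no male breast patients the bracket is s / [s + (1 − s)f].

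| s | f | women overall | share of δ absorbed |
|---|---|---|---|
| 0.20 | 0.50 | 0.20 + 0.80 × 0.50 = 0.60 | 0.20 / 0.60 = 0.33 |
| 1/3 | 0.50 | 0.667 | 0.333 / 0.667 = 0.50 |
| 0.60 | 0.40 | 0.60 + 0.40 × 0.40 = 0.76 | 0.60 / 0.76 = 0.79 |

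If δ = 0 the added term is zero whatever the mix. If γ and δ have opposite signs, they offset each other.

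**False gender findings when γ = 0.** The SE of the gender × X slope is √[1/(264·p) + 1/(264·(1 − p))], where p is the proportion of women.
- s = 0.20, f = 0.50: SE = 0.126. For δ = 0.2 the shift is 0.333 × 0.2 = 0.067, or 0.53 SE, and the rejection rate is about 8%. For δ = 0.3 it is about 13%.
- s = 0.60, f = 0.40: SE = 0.144. For δ = 0.2 the shift is 0.789 × 0.2 = 0.158, or 1.10 SE, and the rejection rate is about 20%. For δ = 0.3 it is about 38%.

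A regression simulation (3,000 runs, n = 264, s = 1/3, f = 0.5) gave spurious slopes of about 0.10 and 0.15 for δ = 0.2 and 0.3. Rejection was about 10–12% and 20–21%, and it stayed at 5% when δ = 0. With breast and breast × X added, the spurious slope returned to about 0 and rejection to 4–6%. A breast main effect without the product term left the spurious slope where it was, because the bias lies in the slope.

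**Cost of separating the two.** Once site and site × X are in the model, the gender contrast rests on the non-breast dyads: 264 × 0.80 = 211 down to 264 × 0.40 = 106. Its SE becomes √[1/(m·f) + 1/(m·(1 − f))], where m is the number of non-breast dyads.
- s = 0.20, f = 0.50: 0.138 against 0.126, ratio √1.2 = 1.10.
- s = 0.60, f = 0.40: 0.199 against 0.144, ratio √1.9 = 1.38.

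The slope difference detectable with 80% power, (1.96 + 0.84) × SE, rises from about 0.35–0.43 to 0.39–0.56 across the assumed mixes.

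All of this is a single-path simplification of the dyadic structural equation model.

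**The case against.** The strongest case against the point is that this is a condensed article. Covariates and sensitivity models may be listed in a full plan that is not shown, and Figure 2, whose legend refers to control variables, cannot be seen. The documents also give no evidence that site or hormone therapy changes the slopes. A pooled gender difference in the enrolled population is a legitimate descriptive answer to the question of for whom the models work. Extra interactions also burden models that the authors already expect may not all be estimable by maximum likelihood.

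Much of this stands. It rules out saying that no adjustment exists anywhere, and it is why the planned models should remain. What survives is that the gender model, as the article describes it, cannot distinguish the two explanations, and that the stated design remedy is aimed at gender and role.

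A reader might infer more in three ways, none of them supported:
- That a breast or hormone-therapy difference will be reported as a male–female difference. This needs a slope difference by site. Even with δ up to 0.3, most studies under the assumed mixes would not declare a false interaction.
- That male partners are mostly partners of breast patients. This depends on the unstated mix: under the assumptions it is 33–79% in opposite-sex couples.
- That the Introduction concedes this problem. It concedes that gender is confounded with patient role in breast-only samples.

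Including both sexes at the other sites also dilutes the confounding even without a site term, since only part of δ is absorbed.

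**Conclusion.** The point holds in conditional form. As described, the gender terms carry part of any breast-versus-other slope difference: 33–79% for breast shares of 20–60% with 40–50% women elsewhere. For assumed slope differences of 0.2 and 0.3, a false gender interaction would arise in about 8–20% and 13–38% of studies instead of 5%. With no slope difference by site there is no bias. The mix and the slope differences are assumptions; the structural link between breast cancer and female patients comes from the article. This is an inexpensive improvement to a named aim, and it does not show that the planned analysis is invalid.

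**What to change.** Keep the planned gender models and prespecify two sensitivity analyses beside them:

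- Repeat the gender interactions in colon, rectal and lung dyads only.
- Where the model can be estimated, add breast versus other site with site × communication and site × mediator terms, in both patient and partner equations. A site main effect alone is not enough.

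Report the three sets of estimates with confidence intervals side by side. Describe a difference as gender-specific, rather than possibly site-related, only in light of all three. No fixed threshold for similar size should be set, because the smaller sample could then suppress a real gender difference.

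The change needs analysis wording only, since site and therapy are already extracted. The cost is precision: standard errors about 10–38% larger under the assumed mixes, with the contrast resting on about 106–211 of 264 dyads. The added terms also enlarge models that may already be hard to fit. Both analyses should therefore be labelled supportive.

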This study is the first comprehensive multi-method longitudinal study of couples’ communication in the context of cancer. The design incorporates key recommendations in the literature (Lepore and Revenson, 2007; Badr et al., 2013): (a) a dyadic approach that includes both partners and treats the couple as the unit of analysis; (b) the inclusion of dyads dealing with different types of cancer, including three cancers that affect both male and female patients so that role can be disentangled from gender; (c) the use of observational methods that enable analysis of interactional patterns and expressed emotional arousal as well as comparisons between these measures and self-report in predicting outcomes; (d) the use of EMAs that can capture the interactional nature of communication processes occurring day-to-day, and the temporal sequencing of communication behaviors, mediating variables and adjustment; and (e) assessment of communication using self-report questionnaires collected four times over the course of 1 year, affording analysis of change in communication patterns and mediators across time.

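### The patient-versus-partner (role) test in Aim 2 names no gender term, so part of any gender difference in a path can appear as, or mask, a role difference

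*Protocol article*

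**What the plan says.** The Introduction faults earlier breast-cancer studies on this point: "Because the majority of breast cancer cases are female, sole focus on this cancer site confounds gender and patient role". It then gives as a strength of the present design that it includes "three cancers that affect both male and female patients so that role can be disentangled from gender".

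Under Design and Participants, eligible patients have "stage II-IV breast, colon, rectal, or lung cancer". No site share, quota or sex balance is stated, and the text itself excepts breast cancer from the sites that are common in both sexes.

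Under Differential Functioning of Social-Cognitive Processing and Relationship Intimacy Models by Gender and Role, the article says "we will employ two different modeling approaches within an APIM framework":

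- Gender: "For gender, we will add gender × communication and gender × mediator" terms to the main-effects models. The examples pair each member's own gender with that member's own communication or intimacy.
- Role: "To examine differential functioning by role, we will examine how individual cross-role equality constraints for parallel APIM actor and partner effects" alter fit, together with tests of between-role differences in indirect effects. No gender term is mentioned.

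The base models, described under Overview and in the questionnaire and EMA subsections, are built "with patients and partners treated as distinguishable dyad members" and name no gender covariate. Exploratory, non-dyadic models in gender and role subsamples supplement the two approaches. The text does not say that gender is crossed with role in them.

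**The concern.** An equality constraint between a patient path and the matching partner path compares two averages, each taken over whatever sex mix that role has. If the mixes differ and the path differs by gender, the constraint can fail when role has no effect at all. It can also hold when a real role effect is offset by gender.

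The Introduction makes this more than theoretical. It suggests that lack of cognitive processing may drive distress more in males, and that patients may feel the effects of buffering more than partners do. If patients are predominantly female, a stronger path in males would make that path look stronger in partners. That could create a false role difference or cancel a true excess in patients. The Discussion says that subgroup differences will inform clinical application, so a misattributed one matters.

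**Working it through.** There is no stated figure to reproduce. The check is algebra plus a simulation.

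**Inputs from the article.** Role test by cross-role constraints with no gender term named; breast cancer eligible with no share given; 264 dyads projected as complete cases (Sample Size and Power).

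**Assumed inputs, not in the article.** Breast share b; female share q at the other sites; 99% of breast patients female; gender gap G in a path; true role difference zero; the same predictor variance in both genders.

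**Step 1, the leak.** Let bF and bM be the female and male slopes, equal in both roles, and let f = P(female | patient). In opposite-sex couples P(female | partner) = 1 − f.

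- Patient average: f·bF + (1 − f)·bM
- Partner average: (1 − f)·bF + f·bM
- Difference: (2f − 1)(bF − bM) = (2f − 1)·G

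Same-sex couples add nothing to this difference, so they dilute it.

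**Step 2, the size.** f = 0.99b + q(1 − b), and the leak as a fraction of G is 2f − 1.

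| b | f (q = 0.50) | leak | f (q = 0.40) | leak |
|---|---|---|---|---|
| 0 | 0.500 | 0 | 0.400 | −0.20 |
| 0.20 | 0.598 | 0.196 | 0.518 | 0.036 |
| 0.30 | 0.647 | 0.294 | 0.577 | 0.154 |
| 0.50 | 0.745 | 0.490 | 0.695 | 0.390 |
| 0.75 | 0.8675 | 0.735 | 0.8425 | 0.685 |

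Example: b = 0.50 and q = 0.50 give 2 × 0.745 − 1 = 0.49. A gender gap of 0.20 then yields a false role gap of 0.49 × 0.20 ≈ 0.10. With q = 0.40 the leak is zero where 0.99b + 0.40(1 − b) = 0.50, that is b = 0.10/0.59 ≈ 0.17.

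**Step 3, the effect on the test.** Simulation of 264 opposite-sex dyads, 3,000 runs, q = 0.50, mean actor slope 0.25, larger slope in males, within-dyad correlation 0.3 for predictors and residuals, true role difference zero. Equality of the patient and partner actor slopes was tested at a nominal 5% with dyad-clustered errors.

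| b | gap 0.20: mean false difference | rejection | gap 0.30: mean false difference | rejection |
|---|---|---|---|---|
| 0 | 0.00 | 5.2% | 0.00 | 5.7% |
| 0.25 | −0.05 | 8.6% | −0.07 | 11.7% |
| 0.50 | −0.10 | 17.8% | −0.15 | 33.5% |
| 0.75 | −0.15 | 34.2% | −0.22 | 62.2% |

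With gender and gender × actor communication added, coded the same way in both roles, the mean false difference was −0.002 to 0.004. Rejection was 4.8% to 7.2%, highest at b = 0.75. This is a single-path, cross-sectional simplification. It shows the mechanism and its order of size, not the operating characteristics of the planned panel or multilevel models.

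**The case against.** The strongest reply is that this reads a defect into silence. The article does not say that gender is left out of the model carrying the role constraints, and a condensed article may leave covariates to a fuller plan. That is fair as far as it goes. But the text sets out the role test specifically, as a separate approach resting on base models with no gender term. As written, it does not use the separation that the mixed sample makes possible. The authors do put gender and role together in the models for vocal fundamental frequency, but do not say so here. The exploratory subsample models do not fill the gap, because they are non-dyadic and not stated to cross the two factors.

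Four stronger readings are tempting and are not supported:

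- **That Aim 2 as a whole cannot separate role from gender.** The gender interactions are estimated within each role, so role does not confound the gender contrast. For actor paths, that same model already holds what is needed to compare roles at the same gender.
- **That patients in this study are mostly female.** No site share or sex mix is given. With a small breast share and mostly male patients at the other sites, the leak is near zero or changes sign.
- **That the design claim is false.** Saying that role can be disentangled describes what the sample allows, and that is true. The shortfall is in the described analysis.
- **That patient gender is also confounded with cancer site.** The two overlap where breast cancer is enrolled, but the article posits no site difference in these paths and the check above does not test one.

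**Conclusion.** The concern holds for the role contrast of Aim 2, in both the constraint tests and the between-role comparison of indirect effects. As described, that contrast absorbs a fraction 2P(female | patient) − 1 of any gender difference in a path. Under the assumed inputs the fraction runs from about 4% (breast share 0.20, other sites 40% female) to about 74% (share 0.75, other sites 50% female). False rejection of role equality is modest at a share of 0.25 (8.6% for a gap of 0.20) and serious at 0.50 and above.

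Whether the bias in this study is material or small cannot be settled from the article, because neither the breast share nor the gender gap is given. Nothing in the described design or analysis keeps it small. The Aim 1 model tests and the gender contrast are not affected.

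**What to change.** State that the cross-role equality constraints, and the between-role differences in indirect effects, are tested in the APIM that already holds the gender interactions. Specifically:

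- Include gender main effects and a gender interaction on every constrained path, partner paths as well as actor paths. The examples in the article cover actor paths only.
- Code gender identically for patients and partners, for instance +½ female and −½ male, so that roles are compared at the same gender. Centring gender at each role's own mean would bring the unadjusted contrast back.
- Repeat the role test without breast-cancer dyads as a sensitivity analysis, keeping the gender terms. Dropping those dyads alone is not a cure: at b = 0 with other sites 40% female, the leak is −20% of G.

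A two-group model split by patient sex would also separate the factors, but is less practical. At b = 0.75 and q = 0.50 only about (1 − 0.8675) × 264 = 35 couples would have a male patient, few for a four-wave model with six communication indicators per member.

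The cost is precision and a somewhat larger model. Treating members as independent, the standard error of the role contrast grows by about 1/√(1 − d²), with d = 2f − 1. For q = 0.50 the factor is 1.02 at b = 0.20 (d = 0.196), 1.15 at b = 0.50 (d = 0.49) and 1.47 at b = 0.75 (d = 0.735). No new data are needed.
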